#### Survey data

The sample size for the survey of women is determined by the need to focus on a fixed period to encourage site compliance with a short-focussed collection period. A collection period of two- three weeks pre- and post-implementation across at least 30 sites each with approximately 2000 births per year will yield a total sample of approximately 2300 with a 50% completion rate (1150 in each period). This will provide approximately 500 women with DFM, 500 women who smoked at booking, and around 600 women with risk factors at term.

The sample size for the survey of healthcare professionals is based on two full time equivalents per 1000 births across all ‘targeted’ implementer sites and 60% availability and a 30% completion rate over the two-week survey period gives a total sample size of 6000 (3000 in each period pre and post implementation).

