**Methods:**

This is a mixed-methods study of maternity services across three Australian states; Queensland, Victoria and New South Wales. The study includes evaluation of ‘targeted’ implementer sites (combined total approximately 113,000 births annually, 50% of births in these states) and monitoring of key outcomes state-wide across all maternity services. Progressive implementation over 2.5 years, managed by state Departments of Health, commenced from mid-2019. This study will determine the impact of implementing the SBB on maternity services and perinatal outcomes, specifically for reducing late gestation stillbirth. Comprehensive process, impact, and outcome evaluations will be conducted using routinely collected perinatal data, pre- and post- implementation surveys, clinical audits, focus group discussions and interviews. Evaluations explore the views and experiences of clinicians embedding the SBB into routine practice as well as women’s experience with care and the acceptability of the initiative.

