### Sample size and data analysis

#### Clinical outcomes

Based on the most recent 3 year period prior to the SBB rollout, for which data are currently available (2016-2018), the late gestation stillbirth rate in Australia was 2.4 per 1000 births (unpublished data Stillbirth CRE). This decreased from 2.7 per 1000 births in 2013-2015 [6]. The SBB initiative aims to amplify and sustain a further rate reduction of at least 20% to target a rate of 1.9 per 1000 births by the end of 2023. Maintaining a downward pressure on rates is challenging given that as rates get lower further reductions may become increasingly more difficult to attain.

Based on 113,000 births per year across ‘targeted’ implementers, the study will be able to estimate a stillbirth rate of 1.9 to a precision of 1.7 to 2.1, with 95% confidence: 430 stillbirths out of 113,000 x 2 =1.9 per 1000 births. Put another way, the project will have 95% power (alpha=5%, two-sided) to show that an achieved stillbirth rate of 1.9 per 1000 births (the target for 2022-2023) is statistically significantly different from a stillbirth rate of 2.4 per 1000 births (pre-implementation for 2016-2018).

Secondary endpoints including obstetric intervention and other important maternal and newborn outcomes measurable using routine data will be analysed using analysis, similar to the pre-specified primary endpoint. Formal power calculations for the secondary endpoints have not been done due to statistical multiplicity. Point estimates for these secondary endpoints will be checked to confirm they are consistent with the result for the primary endpoint. Any outlying results will be investigated. Descriptive statistics will be used to summarise data such as demographic characteristics.

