#### Subgroup analyses

Where sample sizes allow, subgroup analyses by demographic characteristics of the maternity services and level of implementation (for ‘targeted’ implementers, as measured by process indicators and results of the leadership survey) will be undertaken for quantitative clinical endpoints and survey data. Maternity services characteristics to be explored include state, remoteness, private versus public, and service capability level according to the Australian Maternity Services Capability Framework [37]. Subgroup analysis will also explore variations in the provision of antenatal care and disparities in stillbirth rates and other clinical outcomes for Aboriginal and Torres Strait Islander, migrant and refugee, and rural and remote women. Subgroup analysis from the survey of women will be undertaken by parity, maternal age, and pregnancy complications. Subgroup analysis of the healthcare professional survey data will explore the influence of discipline (e.g. midwives, obstetricians).

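### The healthcare professional survey size of 6000 (3000 per period) does not follow from its stated inputs, which give about 41 per period

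*Protocol article*

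**What the plan says.** The section Sample size and data analysis, under Survey data, gives the derivation in one sentence. It starts from the workforce: "The sample size for the survey of healthcare professionals is based on two full time equivalents per 1000 births across all ‘targeted’ implementer sites". It then applies two percentages and states the result: "60% availability and a 30% completion rate over the two-week survey period gives a total sample size of 6000". A parenthesis splits the total: "3000 in each period pre and post implementation".

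The births to which the ratio applies are given twice, consistently. The Abstract (Methods) describes the targeted sites as "combined total approximately 113,000 births annually, 50% of births in these states", and the Clinical outcomes part of the sample size section opens its own calculation with "Based on 113,000 births per year across ‘targeted’ implementers".

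Under Subgroup analyses the article adds: "Subgroup analysis of the healthcare professional survey data will explore the influence of discipline".

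**The concern.** The sentence presents 6000 as the product of its inputs, and the inputs do not produce it. The mismatch is too large for rounding or a loosely worded assumption. A reader therefore cannot tell which survey is planned: one with thousands of respondents per period, which could support comparisons between disciplines, or one with a few dozen, which could not.

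The survey is one of several sources for the third study aim, on change in awareness, knowledge and behaviour among professionals and women. Its before-and-after comparison and its breakdown by discipline both depend on which figure is right.

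**Working it through.** **Inputs, all from the protocol article**

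- Staffing ratio: 2 FTE per 1000 births (Survey data)
- Births at targeted sites: 113,000 per year (Abstract, Methods; Clinical outcomes)
- Availability 60%, completion 30% (Survey data); product 0.60 x 0.30 = 0.18
- Stated result: 3000 per period, 6000 in total (Survey data)

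**Attempt to reproduce the stated figure**

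- FTE at targeted sites: 113 x 2 = 226
- Available: 226 x 0.60 = 135.6
- Completing: 135.6 x 0.30 = 40.7 per period, so 81.4 over both periods
- Ratio of stated to computed: 3000 / 40.7 = 73.7

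The stated figure is not reproduced.

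**Working backwards from 3000**

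- Eligible staff needed: 3000 / 0.18 = 16,667
- Per 1000 births: 16,667 / 113 = 147.5, against the stated 2

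**Other readings tried**

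| Reading | Per period |
|---|---|
| Every FTE available and responding | 226 |
| All births in the three states (113,000 / 0.50 = 226,000) | 452 x 0.18 = 81.4 |
| 1.5 persons per FTE (assumed) | 40.7 x 1.5 = 61 |
| 3 persons per FTE (assumed) | 40.7 x 3 = 122 |
| Ratio misprinted, 2 per 100 births | 2260 x 0.18 = 407 |
| Ratio misprinted, 2 per 10 births | 22,600 x 0.18 = 4068 |

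None gives 3000. The article states no conversion from FTE to persons; about 74 persons per FTE would be needed. One product comes near the total of 6000: 226 FTE x 26 fortnights = 5876. It drops both stated percentages and has no basis in the text, so I treat it as coincidence.

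**Check on the neighbouring calculation**

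The survey of women, in the same part of the article, does reproduce: 30 sites x 2000 births / 52 weeks x 2 weeks x 0.50 = 1154, against the stated 1150. Of the two survey calculations, only the one for healthcare professionals fails.

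**What each figure would mean for precision**

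For a proportion of 50%, the 95% half-width is 1.96 x sqrt(0.25 / n). The smallest before-after difference detectable with 80% power (two-sided 5%, two independent samples) is about 2.8 x sqrt(2 x 0.25 / n).

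| n per period | Half-width | Detectable difference |
|---|---|---|
| 41 | about 15 points | about 31 points |
| 122 | about 9 points | about 18 points |
| 3000 | about 1.8 points | about 3.6 points |

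The first two rows apply only if the staffing ratio is right and the 3000 is wrong.

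**The case against.** The best case on the other side accepts the arithmetic and disputes its consequences. Most of that case stands.

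- The survey is a secondary process and impact component. The primary outcome comes from routine perinatal data and does not use it. The article attaches no test, power or target difference to this survey, so the number is an expected yield. Invitations go to all professionals providing antenatal care at the sites, so it does not cap recruitment either.
- A reader might infer that the evidence for the third aim rests mainly on this survey. The article does not support that: the aim also covers women and draws on the survey of women, interviews and focus groups, and the knowledge and confidence survey before and after eLearning.
- A reader might infer that subgroup results by discipline are promised whatever the yield. The Subgroup analyses section opens by making its analyses of survey data conditional on adequate sample sizes, and the discipline sentence speaks only of exploring.
- A reader might infer that the survey will in fact have about 41 respondents per period. That does not follow. The error may lie in the printed ratio. Invitations also go to people, not FTE, and the article allows distribution through professional colleges, which could reach staff at non-targeted sites.

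None of this rescues the sentence itself. The college route lies outside the stated formula, which is confined to targeted sites, and plausible part-time working moves the result only from 41 to somewhere around 61 to 122.

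**Conclusion.** The concern holds as an internal arithmetic contradiction. The stated inputs give about 41 respondents per period and about 81 in total; the article states 3000 and 6000, about 74 times as many. This rests only on figures printed in the article and on reading the ratio as applying to one year of births at targeted sites. Using all births in the three states, or ignoring non-response entirely, leaves 81 and 226 per period, still far below 3000.

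The document does not show which element is wrong. If 3000 is a sound expectation reached by another route, the survey's precision is unaffected and only the staffing input needs correcting. If the ratio is sound, the before-after comparison could detect only very large changes and could not support comparisons between disciplines. In neither case is the stillbirth analysis touched.

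**What to change.** Rewrite the sentence so that the ratio, the two percentages and the total agree, and print the expected number per period. A direct source would be the head-count of clinicians whom the site teams will invite, multiplied by availability and completion; other sources would serve if stated.

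- If 3000 per period is the real expectation, correct the staffing input. At the stated percentages it must correspond to about 16,667 eligible staff.
- If the number is really of the order of 41 to 122, restate the sample size, give the precision that goes with it, and label the analysis by discipline as descriptive.
- If distribution through professional colleges is meant to contribute, bring it into the calculation explicitly, since the present formula covers targeted sites only.

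The cost is one corrected sentence, plus a short statement of precision if the smaller number applies. No change to the design or to data collection is needed.

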#### Focus groups and interviews

Thematic analysis [36] will be applied to the qualitative data collected throughout the study. NVivo software will be used to manage the qualitative data and to facilitate coding and development of themes. At least two researchers will read transcripts and independently establish coding categories before using an iterative approach to develop agreed themes and subthemes, with attention to contrasts across groups. Concordance across coders will be reviewed and discrepancies will be discussed to ensure conceptual consistency. Throughout the analysis, themes will be reviewed and discussed with members of the wider research team to include clinician, non-clinician and consumer perspectives and to strengthen the credibility and trustworthiness of findings.

#### Subgroup analyses

Where sample sizes allow, subgroup analyses by demographic characteristics of the maternity services and level of implementation (for ‘targeted’ implementers, as measured by process indicators and results of the leadership survey) will be undertaken for quantitative clinical endpoints and survey data. Maternity services characteristics to be explored include state, remoteness, private versus public, and service capability level according to the Australian Maternity Services Capability Framework [37]. Subgroup analysis will also explore variations in the provision of antenatal care and disparities in stillbirth rates and other clinical outcomes for Aboriginal and Torres Strait Islander, migrant and refugee, and rural and remote women. Subgroup analysis from the survey of women will be undertaken by parity, maternal age, and pregnancy complications. Subgroup analysis of the healthcare professional survey data will explore the influence of discipline (e.g. midwives, obstetricians).

### Data storage, access and archive

To ensure confidentiality, data will be stored securely on a password protected web-based database with access restricted to the research team only. Electronic files will be stored on secure password protected drives on the Mater Research Institute (MRI) network. Any associated paper copies of documentation will be kept in a locked secure environment by the Chief Investigator at MRI, Brisbane.

Data will be kept for a period of 7 years after the conclusion of the study, in accordance with institutional policies. The Mater Research Ownership, Storage and Retention of Human Research Materials and Data Policy (PY-RSH_300300) requires that permission from the Head of Department where the Chief investigator is employed should be obtained before moving or destroying the research data once the primary period of retention has finished.

### SBB study committees and advisory groups

An SBB Steering committee, made up of Stillbirth CRE representatives, leads from each jurisdictional partner organisation and a parent representative will meet quarterly to provide high level oversight for the SBB program. An operational committee, made up of the study chief, associate and partner investigators, and jurisdictional implementation team representatives will meet regularly to ensure successful implementation of the SBB. Overarching advice and support specific to consultation with Aboriginal and Torres Strait Islander, and migrant and refugee women (and their care providers) will be sought through the Stillbirth CRE Aboriginal and Torres Strait Islander and Migrant and Refugee Advisory Groups. The Stillbirth CRE Aboriginal and Torres Strait Islander Advisory Group follow the Guidelines for Ethical Research in Australian Indigenous Studies (Australian Institute of Aboriginal and Torres Strait Islander Studies) and relevant NHMRC ethical guidelines for research with Aboriginal and Torres Strait Islander Peoples [38].

### Dissemination plan

The final data analysis examining the change in stillbirth rates will commence once all the PDC data for each participating state has been submitted (Dec 2023). Some preliminary analysis of historical data (15 years pre-implementation) will begin once appropriate approvals are obtained and results will be presented at SBB dissemination events held annually (Stillbirth CRE Annual National Forum). These forums are open to maternity healthcare professionals, consumer representatives, policy makers and researchers from around the country to ensure wide audience is captured. Annual forums will also provide a platform for the Stillbirth CRE and Department of Health partners to report benchmarking for selected indicators throughout the study. Following data analysis, a comprehensive national report will be drafted which summarises the aggregate data. High-level aggregate data will be presented, and individual services will not be identifiable. In addition to clinical outcomes, this report will contain aggregate data from ‘targeted’ implementers for key process and impact measures relating to each element of the SBB. The final evaluation report is due to be submitted by July 2024.

Results of the study will also be submitted to peer reviewed journals for publication, presented at leading national and international professional conferences and further disseminated to the public and healthcare community, to raise awareness and inform best clinical practice in the prevention of stillbirth.

## Discussion

Stillbirth is a devastating pregnancy outcome resulting in profound and often long-lasting adverse psychosocial effects for the mother, father and family. Late gestation stillbith rates in Australia are unacceptably high. Through the Stillbirth CRE, we have established a critical mass of world-renowned experts in stillbirth prevention. Working in partnership with parents, we are in a unique position to significantly reduce the incidence of stillbirth. We have identified key evidence practice gaps in maternity care in stillbirth prevention and there is strong evidence on how to overcome these in several key areas. The challenge now is to translate the evidence into practice, and this is what the SBB for Australia will do.

Partnership with parent support and advocate organisations (Stillbirth Foundation Australia, Still Aware, and others) will ensure the voices of parents are heard through engaging parents and the community in development of materials and implementation strategies.

Our partnering state health department organisations share the Stillbirth CRE’s strong desire to reduce stillbirth rates and other adverse pregnancy outcomes by reducing gaps between evidence and practice in maternity care. These partners are the peak authorities for leading quality improvement in maternity health care for their jurisdictions. They formulate and disseminate policies that have a significant impact on health care services and delivery and are at the forefront of translation of health and policy practice. They will actively promote and support the SBB rollout across all maternity services in their jurisdictions, shaping the care practices recommended into policy. Initial rollout involves targeted support to those maternity hospitals recruited to each states SBB implementation programs. An in depth understanding of the factors which underpin successful implementation of the SBB in these services will guide future implementation activities and refinement of the SBB. As will insights into the added value of differing approaches to support implementation.

The Stillbirth CRE is working to upscale the SBB initiative across Australia and partnering with health departments of all remaining jurisdictions to commence implementing the SBB over 2020 to 2021. Implementation and evaluation across these other states/territories will vary and will be incorporated into a future planned national evaluation. We anticipate the SBB initiative will save the lives of over 150 babies each year if up scaled across all Australian jurisdictions. The findings of this study will also provide evidence for the value of a systematic, while pragmatic, approach to strategies to reduce the evidence-practice gaps across maternity services.

## Data Availability

The datasets used during the current study are available from the corresponding author upon reasonable request.

## Abbreviations

CEC: Clinical Excellence Commission
CEQ: Clinical Excellence Queensland
CTG: Cardiotocography
DFM: Decreased fetal movements
FGR: Fetal growth restriction
ICHOM: International Consortium for Health Outcomes Measurement
MCQIC: The Scottish Maternity and Children Quality Improvement Collaborative
NHMRC: National Health and Medical Research Council
NSW: New South Wales
PSANZ: Perinatal Society of Australia and New Zealand
QLD: Queensland
SBB: Safer Baby Bundle
SBLCB: Saving Babies Lives Care Bundle
SCV: Safer Care Victoria
SFH: Symphyseal-fundal height
Stillbirth CRE: The Centre of Research Excellence in Stillbirth
UK: United Kingdom
VIC: Victoria
